## Abstract

**Background:**

Fibromyalgia is a multidimensional disorder for which treatment as yet remains unsatisfactory. Studies of an acupuncture-based approach, despite its broad acceptance among patients and healthcare staff, have not produced sufficient evidence of its effectiveness in treating this syndrome. The present study aims to evaluate the effectiveness of individualized acupuncture for patients with fibromyalgia, with respect to reducing their pain and level of incapacity, and improving their quality of life.

**Methods/design:**

Randomized controlled multicentre study, with 156 outpatients, aged over 17 years, diagnosed with fibromyalgia according to American College of Rheumatology criteria, either alone or associated with severe depression, according to the criteria of the Diagnostic and Statistical Manual for Mental Disorders. The participants will be randomly assigned to receive either "True acupuncture" or "Sham acupuncture". They will be evaluated using a specific measurement system, constituted of the Fibromyalgia Impact Questionnaire and the Hamilton rating scale for depression. Also taken into consideration will be the clinical and subjective pain intensity, the patient's family structure and relationships, psychological aspects, quality of life, the duration of previous temporary disability, the consumption of antidepressant, analgesic and anti-inflammatory medication, and the potential effect of factors considered to be predictors of a poor prognosis. All these aspects will be examined by questionnaires and other suitably-validated instruments. The results obtained will be analysed at 10 weeks, and 6 and 12 months from the start of treatment.

**Discussion:**

This trial will utilize high quality trial methodologies in accordance with CONSORT guidelines. It may provide evidence for the effectiveness of acupuncture as a treatment for fibromyalgia either alone or associated with severe depression.

**Trial registration:**

ISRCTN trial number ISRCTN60217348 (19 October 2010)

## Background

The etiopathogeny of fibromyalgia syndrome (FMS) remains unknown, although current hypotheses centre on anomalous peripheral nociception caused by wind-up, central sensitivization, high levels of substance P and neurotrophins, and alterations to the hypothalamus-hypophysis-adrenal axis [1,2].

It is a multidimensional disorder, with currently poor therapeutic results. Despite the considerable increase in the number of studies published from 2000 to 2010, current treatment protocols are still unable to resolve the persistent symptoms experienced or improve the functional limitations and quality of life of these patients [3].

The prevalence of FMS among the Spanish population has been estimated at 2.7%, but at 4.2% for women and 0.2% for men [4]. Factors that may raise the risk of FMS include middle age, early school leaving and low family income.

Levels of anxiety and depression among patients with musculoskeletal pain are known to be related to FMS [5]; thus, the prevalence of patients with FMS and severe depression varies from 20-80% [6].

Pharmacological treatment continues to be the chief treatment option; in this respect, an important role is played by tricyclic antidepressants, which have a direct effect on the reuptake of serotonin and norepinephrine, thus improving sleep patterns and alleviating depression, stress and anxiety, as well as inhibiting pain pathways and recognition [7], although they have only been proved to be moderately effective [8,9]. Studies with new dual serotonin-norepinephrine reuptake inhibitors have produced promising preliminary results [10-12]. In addition, pregabalin has produced improvements, in comparison to a placebo, with respect to the treatment of pain, asthenia and sleep disorders among patients with FMS [13], and the combination of paracetamol and tramadol has also been found to be beneficial [14,15]. These approaches, thus, are opening up new possibilities in the pharmacological treatment of FMS syndrome. New contributions to our understanding of the etiopathogenic mechanism of FMS are orienting treatment toward improving central sensitivization, for example via antagonists of N-Methyl-D-aspartate (NMDA) receptors [16].

Non-pharmacological options include aerobic exercise, and muscle toning and stretching [3,17], which activate anti-nociceptive mechanisms and achieve pain reduction. There is moderate evidence that aerobic exercise is more beneficial than flexibilization, but no evidence that any one type of exercise is superior to another [18]. Cognitive-behavioural therapy has proved to be effective for alleviating symptoms and pain-related behavioural disorders, by improving central sensitization and activating anti-nociceptive mechanisms [19,20].

Acupuncture has been used as a treatment option in China for over 2000 years [21] and is increasingly accepted in the West, where its use has become considerably more common in recent decades, especially for pathologies producing high levels of pain [22,23], and thus it has been suggested as a remedy for FMS [23,24].

According to traditional Chinese medicine, FMS results from an imbalance that blocks or exhausts a person's internal energy (*Qi*) and the flow of blood, giving rise to the appearance of the symptoms that are characteristic of this syndrome [25,26].

Despite the broad acceptance of acupuncture among patients and healthcare staff, the studies conducted to date have not produced sufficient evidence of its effectiveness in treating FMS [27], although the latest systematic reviews have shown these studies to be of low quality [17,28,29]. Since the last of these published reviews, in June 2004 [27], various other studies, of higher quality, have been conducted, but the results they report are uneven, and thus little light is shed upon the role of acupuncture in treating FMS. One well-designed study [30] randomised 100 FMS patients into among four groups (one given true acupuncture, and the other three, sham acupuncture), with two sessions per week being given for 12 weeks. No differences were found among any of the outcome measures, but this is not surprising, as the authors used a standard prescription of acupuncture points, which is not the correct procedure [31]. Similar results have been found in another study, also well designed, which concluded that the level of analgesia attained is independent of the location of the acupuncture needles [32]. On the contrary, another well-designed study [33] obtained positive results on comparing real acupuncture with a placebo in terms of relieving pain, asthenia and anxiety, with a reduction of 7 points on the scale of the Fibromyalgia Impact Questionnaire. Another study, carried out in 2008, also reported a reduction in pain intensity and an improvement in quality of life, three months after acupuncture treatment was applied to a group of FMS patients, in comparison with tricyclic antidepressant treatment and exercise [34]. Acupuncture appears to be both safe and effective in treating depression, and is comparable with antidepressant treatment [35].

In view of these data, we designed this randomized controlled multicentre study of FMS patients, with the aim of determining the effectiveness of traditional acupuncture, using a point-selection algorithm established on the basis of the particular characteristics of each patient (seeking to reproduce standard clinical practice), and evaluating the progression of the illness using a specific measurement system, following OMERACT recommendations [36], and evaluating levels of depression, clinical and subjective pain intensity, the family life cycle, psychological aspects, quality of life, the duration of short-term disability, the consumption of anti-depressant, analgesic and anti-inflammatory medication, and the potential effect of factors considered to be predictors of a poor prognosis [37].

## Methods

### Trial objectives

The primary objective of the trial is to evaluate the effectiveness, in terms of pain reduction (measured on a 0-100 mm visual analogue scale) achieved at 10 weeks after beginning treatment. The secondary objectives of the trial are 1) to evaluate the effectiveness, in terms of reducing levels of depression (measured on the Hamilton scale, HAMD) at 10 weeks and 6 months after beginning treatment; 2) to evaluate the effectiveness, in terms of improvement measured by the Fibromyalgia Impact Questionnaire (FIQ), at 10 weeks, and 6 and 12 months after beginning treatment, with respect to both the overall value and the subscales of physical function, tiredness, depression and anxiety; 3) to evaluate the effectiveness in terms of reduced pain intensity (measured on a 0-100 mm visual analogue scale) at 6 and 12 months after beginning treatment; 4) to evaluate the effectiveness in terms of improvement perceived by the FMS patient at the end of the treatment; 5) to evaluate the effects on duration of the incapacity for work; 6) to analyse the number and the threshold of tender points perceived by FMS patients, and the changes in this respect after treatment; 7) to evaluate the effectiveness in terms of reduced consumption of anti-depressant, analgesic and anti-inflammatory medication; 8) to describe the family structure, the relation among family members and the family life cycle of FMS patients (genogram); 9) to evaluate the effectiveness in terms of improved health-related quality of life (SF 12); 10) to evaluate the cost-benefit aspect of acupuncture treatment for FMS patients.

### Hypothesis

Acupuncture is capable of reducing the pain felt by patients with fibromyalgia (FMS), whether in simple form or associated with severe depression, to a greater degree than is sham acupuncture. Furthermore, the application of this technique raises the patient's sense of wellbeing, reduces levels of depression, alleviates dysfunction, enhances health-related quality of life and moderates the consumption of drugs used in conventional treatment, thus reducing the negative effects produced by treatment without itself producing any clinically important iatrogeny.

### Design

Controlled multicentre prospective study, with random assignation to receive individualized acupuncture (according to traditional practice and individual diagnosis) or sham acupuncture (control group) with a 1:1 allocation ratio (Figure 1). Patients will be stratified according to level of depression and by treatment centre, and will be blinded to both types of treatment. The evaluation of patients and the analysis of results will be performed by professionals blinded to the assignation of treatment options.

**Figure 1 F1:**
[figure not shown]
**Flow diagram for the study**. Work scheme with description of assessment visits and times.

### Study period

October 2010 - December 2013. At present, no patients have been recruited.

### Setting and participants

Outpatients, aged over 17 years, referred by their GPs to one of three primary healthcare centres participating in the study, and belonging to the Andalusian Public Health System. These will be patients diagnosed with FMS according to the criteria of the American College of Rheumatology (ACR) [38], and who have not previously received acupuncture treatment. The Hamilton scale (HAMD) will be used to stratify the patients into two sub-groups (cut-off point: 21), with or without severe depression.

The patients will be informed as follows: "This study will compare two types of acupuncture. One of them is similar to traditional Chinese acupuncture. The other does not follow these principles, but both types have been associated with positive results in different clinical studies". The patients will also be informed of the possible risks associated with the different types of acupuncture (infection, fainting or bruising) and that they may conclude their participation in the study at any time, without suffering any penalty or loss of benefits to which they would otherwise be entitled.

Any patient suffering pain for any reason other than FMS, or using anticoagulants or opiates, or who is pregnant or a nursing mother, or who is involved in occupational litigation for reasons involving FMS, will be excluded from this study.

### Sample size

The sample size is set at n = 56 patients in each group, for a significance level of 5%, a power of 90% and a difference in the mean pain intensity - according to 0-100 mm VAS - between the real and the sham acupuncture groups of 20.2 points, assuming equal variances (standard deviation = 32.4 points), taking into account the results of an earlier pilot experiment, carried out from April to December 2008. Assuming a dropout rate of 25%, the sample size will thus be n = 75 for each group (n = 78 to adjust by strata). These calculations were performed using the SamplePower 2 program [39].

### Recruitment of patients

The patients are referred by their GPs, in the areas where the study is performed. We have designed a data-compilation form containing the variables of interest, and this will be completed by the corresponding researcher at each centre. At each centre, the information obtained will be recorded on an electronic database, for subsequent statistical analysis.

### Randomisation

The randomisation of the two branches of this study will be performed in a centralised way, allocating the participants with stratification by centre and depression diagnosis and blocking following a 1:1 allocation ratio. The healthcare professionals participating in the study will not take part in the randomisation process. Those patients who meet the criteria for inclusion and who provide written informed consent will be included in the study. Following their inclusion, the researcher will contact the randomisation centre where the patient is registered, and the physician will be informed, by telephone and by fax, of the patient's assignation to one of the two study branches. This procedure ensures that the randomisation is not influenced by the researchers taking part in this study.

### Treatment

The patients taking part in the study will each receive nine acupuncture sessions (one per week), either real or sham, as follows:

a) **Real acupuncture**: Individualised acupuncture, using single-use sterile needles of diverse calibres and lengths. Guidelines have been agreed regarding the selection of points (Table 1). The physician will perform a prior diagnosis, in accordance with the principles of Traditional Chinese Medicine, before selecting the points for the treatment session, taking note of the diagnosis, the acupuncture points selected and the techniques employed.

**Table 1 T1:** Procedure agreed upon for the selection of acupuncture points*

Basic syndrome	Supine	Prone	
Liver-Spleen disharmony	LI4 ↓	BL18 ↓	
	PC6 ↓	BL20 ↑	
	SP6 ↑	SP6 ↑	
	LR3 ↓	GB34 →	

**Associated syndrome**			**Left/Right**

Yin Deficiency and Empty Heat	Add KI6	Add BL23	

Spleen and Kidney Yang Deficiency	Add ST36	Add BL23	

Kidney Yin and Yang Deficiency	Add CV6	Add 52V	

Rising Liver Fire	Replace LR3 with LR2	Replace BL18 with LR2	

Phlegm	Add ST40 CV12	Add BL21	

Wet Heat	Add SP9	Add LI11	

Stomach and intestines	Add ST25	Add BL25 or BL21	

Bladder	Add CV3	Add BL28	

Genitals	Add CV2	Add BL31	

Associated pruritis	Add LR5		

Blood Stasis	Add SP10	Add BL17	

**Additional symptoms**			

Anxiety	Yintang		

Depression	GV20		

Severe asthenia	ST36 SP3		

Irritability	PC6		

Insomnia	HT7		

Chest tightness	CV17 PC6		

Inhibited sexual desire	GV4		

Nicturia	BL52		

Pollakisuria	CV3		

Mushy stool	SP9		

Night sweats	HT6		

Severe generalised pain	SP21		

Occipital headache	GB20		

Vertex headache	GV20		

Temporoparietal headache	Taiyang		

Neck pain	GB20 GB21		

Back pain	SI12		

Brachialgia	LI10		

Lumbalgia	BL23 BL25		

Pain in the hip/trochanter	GB30 GB29		

*: Standard acupuncture points for treatment of these symptoms [31]

The treatment will be performed after sterilizing the skin on the areas where the needles will be inserted, and with the patient lying face up or face down. A vertical puncture will be made, unless otherwise indicated, to the depth predetermined for each point (normally between 8-30 mm, depending on the location of the point). Following insertion, stimulation of the acupuncture point will be performed using of bidirectional rotation of the needle sleeve, to achieve the sensation known as *Deqi*, which is commonly described as a 'glowing' feeling. The needle will be maintained in place for 20 minutes, with bidirectional rotation of the needle sleeve (with amplitude and rotation speed as stipulated previously) for one minute, every five minutes (a total of four such rotations per session). Following the treatment session, the needles will be withdrawn. Before each session, the physician will re-evaluate the patient to determine whether his/her clinical situation has changed; if so, the selection of acupuncture points will be reconsidered.

B) **Sham acupuncture**: With the patient lying face down, the insertion of needles into the back and lower back will be simulated. This is a technique, validated previously [40], in which, after sterilization of the surrounding skin, a momentary pressure is exerted using a plastic guide tube through the centre of which a blunt steel rod is inserted, producing the sensation that a puncture has been made, at each of the following points. This plastic guide tube will be presented in containers identical to those used for the real acupuncture group. The patient should remain face down for the 20 minutes of the session, so that the placebo technique remains concealed. Every five minutes, the physician applying the treatment will repeat the action at the corresponding eight points (which are not acupuncture points [31]):

1. Located bilaterally at 1 cm from the spinal apophysis of T3

2. Located bilaterally at 1 cm from the spinal apophysis of T5

3. Located bilaterally at 1 cm from the spinal apophysis of L2

4. Located bilaterally at 1 cm from the spinal apophysis of L5

The same time will be dedicated to the patients in each of the treatment groups; similarly, the time employed for the pre and post-session evaluations will be identical in every case. The healthcare personnel applying the different acupuncture treatments have received at least 300 hours training in the field and have over three years practical experience. All adverse reactions or side effects that may occur will be recorded in the Data Record Book, with a detailed account of the circumstances and the date of occurrence. No relative or other person accompanying the patients in this study will be allowed to enter the treatment room.

### Data collection

The data required for evaluating the effectiveness of the treatment will be collected at baseline and 10 weeks, 6 and 12 months after the intervention has begun, for both groups. Data will be obtained via interviews, self-applied questionnaires, and physical measurements. Data collection instruments and the study timeline are summarised in Table 2.

**Table 2 T2:** Data collection instruments at different assessment points

Variable	T0	2s	3s	4s	5s	6s	7s	8s	9s	T1	T2	T3
*HAMD*	X									X	X	

*FIQ*	X									X	X	X

*0-100 mm VAS*	X									X	X	X

*SF12*	X									X	X	X

*Genogram*	X											

*Tender points count*	X									X	X	X

*Pain threshold*	X									X	X	X

*Improvement perceived by patient*										X		

*Expectations and credibility*			X							X		

*Side effects*										X		

*Diagnosis by traditional Chinese medicine*	X									X		

*Medication consumed*	X									X		

*Occupational data*	X									X	X	X

*Sociodemographic data*	X											

VAS: Pain intensity measured on a visual analogue scale; HAMD: Hamilton scale; FIQ: Fibromyalgia Impact Questionnaire; T0: Baseline value; T1: Final value (10 weeks after start of treatment); T2: Follow-up evaluation 1 (6 months after start of treatment); T3: Follow-up evaluation 2 (12 months after start of treatment); #s: Session number.

A data collection form has been designed, to include the variables of interest, which will be completed by the corresponding researcher at each centre. At each centre, the information obtained will be recorded on an electronic database, for subsequent statistical analysis.

The baseline values (T0), those for the results after 10 weeks (T1) and the follow-up results at 6 and 12 months (T2 and T3) will be determined by evaluators who are blinded to the treatment assignation groups. These same evaluators will provide any necessary assistance regarding the self-administered questionnaires. The Hamilton scale will be applied by specialists in the field, who will also be blinded to the treatment assignation groups.

### Outcomes

#### Primary outcome

Changes in pain intensity, measured on a visual analogue scale, at the end of treatment. The construction validity and reliability of this scale have been proven in previous studies [41-43]. The scale measures a continuous quantitative variable varying from 0 (absence of pain) to 100 (the worst pain imaginable).

#### Secondary outcomes

- Changes in levels of depression, measured on the Hamilton hetero-evaluation scale, at the end of treatment and after 6 months. This scale is of proven discriminant validity, reliability, and sensitivity to change; moreover, it has been validated for use in Spain [44]. It consists of 17 items. Each question has from three to five possible responses, with scores varying from 0-2 to 0-4, respectively. The total score varies from 0-52. To evaluate the response to treatment, a full response is defined as a reduction of 50% or more in the initial score obtained on the scale; a partial response is taken as a reduction of 25-49%, and absence of response is defined as a reduction of less than 25%. Remission is considered to have been achieved with a score of 7 or less, although according to some studies this cut-off point should be lower [45].

- Changes in the overall indicator value and in the different subscales of the Spanish version of the Fibromyalgia Impact Questionnaire [46], at the end of treatment (10 weeks after the start), and at 6 and 12 months from the start of treatment. This is a self-administered questionnaire that measures the aspects of health most affected by FMS during the previous week [47]. It is comprised of ten items, with three questions valued on a Likert scale, and a further seven questions valued on a visual analogue scale, varying from 0 to 10, with the higher scores reflecting a greater negative impact or more severe symptoms.

- Changes in pain intensity on a visual analogue scale, measured at the end of treatment, and at 6 and 12 months after beginning treatment.

- Changes in the pain threshold and number of tender points detected by experienced evaluators, assigned one per centre and non-interchangeable, using a digital pressure algometer with a contact point of 1 cm^2 ^(NIDEC SHIMPO - FGE-100 X - Digital Force Gauge). The pressure applied is 1 kg/s at each of the 18 tender points specified [48]. The patients will be asked to tell the researcher when the sensation of pressure changes to one of pain. From all of these pain points, a mean threshold will be calculated. Normal subjects begin to perceive pain at a pressure of 4 kg [38]. The baseline measurements will be compared with those obtained at the end of treatment, and after 6 and 12 months.

- Improvement perceived by the patient [49], measured on a seven-point Likert scale. "How satisfied are you with your recent treatment for fibromyalgia?" 1 = Extremely satisfied; 2 = Very satisfied; 3 = Moderately satisfied; 4 = Indifferent (an approximately equal degree of satisfaction and dissatisfaction); 5 = Moderately dissatisfied; 6 = Very dissatisfied; 7 = Extremely dissatisfied.

- Changes in patient's health-related quality of life, according to the SF-12 Version 2 Questionnaire. This is a generic questionnaire, derived from SF-36, and validated for Spain [50]. Version 2 enables the researcher to calculate the patient's quality of life in eight dimensions (physical function, physical role, pain, general health, vitality, social function, emotional role and mental health) and two summary components (physical and mental), scale 0-100; lower scores indicate poorer quality of life.

- Consumption of medication. Anti-depressant, analgesic and NSAIDs medication consumed (whether or not prescribed by the patient's doctor) at the moment of randomisation and at follow up (at each treatment session, at the end of treatment and at 6 and 12 months), measured on a four-point Likert scale: 0 = no medication; 1 = less than the usual dose; 2 = daily, at the usual dose; 3 = greater than the usual dose. A record will also be made, by the evaluator, of the names of the pharmaceutical preparations taken by the patient, and the daily dose.

- Expectations and credibility of the treatment [51]. These will be measured using an original scale devised by Borkovec and Nau [52], with four items measuring the following on a continuous visual analogue scale from 0 to 10 (0 = totally disagree, to 10 = totally agree): (1) Do you believe this treatment will alleviate the pain you feel?, (2)Do you believe this treatment to be a logical one?, (3) Would you recommend this treatment to a friend or relative suffering from the same problem?, (4) Do you believe this treatment would be a useful option for dealing with other problems? Items 1 and 2 will be evaluated after the second treatment session, and items 3 and 4 after the eighth session.

- Side effects and adverse reactions. A record will be made of the side effects and possible adverse reactions arising from the treatment.

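### HAMD remission and response are defined with no baseline condition, although eligibility sets no minimum HAMD score, so patients who enter at 7 or less can be counted as remissions without improving

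*Protocol article*

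**What the plan says.** **Who is enrolled.** The abstract describes patients with fibromyalgia "either alone or associated with severe depression". Under Setting and participants, HAMD has one role at entry: "The Hamilton scale (HAMD) will be used to stratify the patients into two sub-groups (cut-off point: 21), with or without severe depression". The exclusions in that section concern other causes of pain, certain drugs, pregnancy or nursing, and litigation. None refers to a low HAMD score.

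**What is measured.** The depression outcome in Secondary outcomes is "Changes in levels of depression, measured on the Hamilton hetero-evaluation scale, at the end of treatment and after 6 months". On the scale, "The total score varies from 0-52". Table 2 schedules HAMD at T0, T1 and T2 without restriction by stratum.

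**How response is judged.** The same paragraph then fixes categories for evaluating response to treatment: "a full response is defined as a reduction of 50% or more in the initial score obtained on the scale"; partial response is a fall of 25 to 49%, and non-response a smaller fall. For remission, "Remission is considered to have been achieved with a score of 7 or less". The only qualification is that some studies would set that cut-off lower.

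**How it is analysed.** The Statistics section specifies an intention-to-treat analysis of all randomised patients and a per-protocol analysis. The baseline-adjusted regression model is described only for pain intensity.

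**The concern.** Remission and percentage response describe a course that starts from a raised score. Here the scale is applied to everyone, and eligibility leaves the lower end open. A patient who starts below the remission cut-off meets the definition on the first day. For a low starting score, half of it is a change of one to three points, which ordinary variation between two ratings can produce.

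Reducing depression is the first secondary objective, and readers tend to find response and remission rates easier to interpret than a mean change. If the rules are applied to all randomised patients, the rates mix improvement with patients who had nothing to remit and with noise at low baselines. The difference between arms is then pulled towards zero.

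**Working it through.** **The plan's own figure.** The article gives no event rate, sample size or power for HAMD response or remission, so there is none to reproduce. Its sample size is for pain: a difference of 20.2 and SD of 32.4, with two-sided 5% alpha and 90% power, give 55.04 per group by the t-test formula, rounded up to 56. Then 56/(1 − 0.25) = 74.7, that is 75. Both match the article, and neither depends on HAMD.

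**Step 1: apply the rules to each baseline b (no assumptions).** Full response needs a fall of at least 0.5 × b, rounded up to a whole point. Remission needs a fall of max(0, b − 7).

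| Baseline HAMD | Fall needed for full response | Fall needed for remission |
|---|---|---|
| 0 | undefined | 0 |
| 1–2 | 1 | 0 |
| 3–4 | 2 | 0 |
| 5–6 | 3 | 0 |
| 7 | 4 | 0 |
| 8 | 4 | 1 |
| 21 | 11 | 14 |

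A patient who worsens from 3 to 7 is also a remission.

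**Step 2: share of patients affected (assumed).** No baseline HAMD distribution is given. Suppose half of the 156 patients (78) are in the lower stratum and 20 to 40% of them start at 7 or less. That is 78 × 0.20 = 16 to 78 × 0.40 = 31 patients, or 10 to 20% of the trial. The Background cites 20 to 80% for severe depression in fibromyalgia. Across that range, with the same 20 to 40%, the count runs from 156 × 0.20 × 0.20 = 6 (4%) to 156 × 0.80 × 0.40 = 50 (32%).

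**Step 3: dilution of the remission difference (assumed rates).** Let s be the share starting at 7 or less. Assume that all of them stay there in both arms, and that remission among the rest is 20% with sham and 40% with real acupuncture. The observed rates are s + (1 − s) × 0.20 and s + (1 − s) × 0.40, so the observed difference is (1 − s) × 20 points. The last column shows the same comparison restricted to patients above 7, with n = 78 × (1 − s) per arm rounded down. Power uses the normal approximation for two proportions at two-sided 5%, before dropout.

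| s | Sham | Real | Difference (points) | Power, all 78 per arm | Power, baseline above 7 only |
|---|---|---|---|---|---|
| 0% | 20.0% | 40.0% | 20.0 | 78% | 78% (n = 78) |
| 4% | 23.2% | 42.4% | 19.2 | 73% | 76% (n = 74) |
| 10% | 28.0% | 46.0% | 18.0 | 65% | 74% (n = 70) |
| 20% | 36.0% | 52.0% | 16.0 | 52% | 69% (n = 62) |
| 32% | 45.6% | 59.2% | 13.6 | 40% | 62% (n = 53) |

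Under these assumptions the restricted denominator keeps more power than the full one, despite fewer patients.

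**Step 4: chance full responses (assumed SD of change, no true change).** For whole-number scores, P = 1 − Φ((fall needed − 0.5)/SD).

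| Baseline | SD 2 | SD 3 | SD 4 |
|---|---|---|---|
| 4 | 23% | 31% | 35% |
| 6 | 11% | 20% | 27% |
| 8 | 4% | 12% | 19% |
| 21 | <0.1% | <0.1% | 0.4% |

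For example, at baseline 6 with SD 3: (3 − 0.5)/3 = 0.83, which gives 20%.

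**The case against.** The best defence is that the declared outcome is change in HAMD score. The objective and the outcome are both worded that way. No section names a remission or response rate as an endpoint to be compared between arms, or says that it will be computed over all 156 patients. The intention-to-treat statement is general. Speaking of remission presupposes someone with depression to remit, and the denominator could be left to a fuller plan. Randomisation is stratified at HAMD 21, and in the severe stratum no patient starts at 7 or less.

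Much of this stands. The change score is untouched, and the article does not commit to a denominator. But the article does more than stay silent: it fixes numerical rules and introduces them as the way to evaluate response. A fuller plan that followed them faithfully would carry the misclassification forward. Stratification does not cure it either, because the lower stratum puts scores of 0 to 7 together with moderate scores.

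Three stronger readings are tempting and not supported:

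- A reader might infer that the trial enrols non-depressed patients in known numbers. The article says only that some patients are without severe depression. Scores of 0 to 7 are eligible, but their frequency is unknown.
- A reader might infer that the whole depression result is compromised or tilted towards one arm. The rules act on both arms alike, so the expected effect is mainly dilution and misclassification.
- A reader might infer that both rates must be confined to the severe stratum. That would discard patients between 8 and the stratum cut-off, who can genuinely respond or remit.

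**Conclusion.** The point holds in limited form. With no minimum HAMD at entry and no baseline condition in the definitions, the response and remission categories misclassify patients with low starting scores. Step 1 establishes this from the article's text alone.

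The size cannot be established from the article. If 10 to 20% of all patients start at 7 or less and stay there, a true 20-point remission difference shows as about 18 to 16 points. Over the wider range of 4 to 32% it shows as about 19 to 14 points. The shares, the 20% and 40% remission rates and the SDs of change are all assumptions. The effect is confined to derived categories of a secondary outcome and does not reach the pain endpoint, the sample size or the HAMD change score.

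**What to change.** State four things alongside the HAMD definitions:

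1. The depression analysis is the HAMD score at T1 and at T2 in all patients, adjusted for T0 HAMD.
2. Remission is computed only among patients with T0 HAMD of 8 or more.
3. The percentage-response categories use the same floor, which also removes the undefined case at a baseline of 0.
4. The denominator is reported per arm for each rate. Results in the severe-depression stratum can be shown as well.

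This takes a few sentences and no new data, since HAMD is already collected at T0, T1 and T2. The article states that no patients had been recruited, so on that status the rule can be set before any data are seen. The cost is a smaller denominator for the two rates. The floor does not remove all noise: at a baseline of 8, with an assumed SD of 3, about 12% would still be full responders by chance. That is a further reason to rest the depression conclusion on the adjusted score.
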